Drawing on theories of network diffusion and social influence, and known patient-level, non-structural barriers (poor CC knowledge; stigma and misconceptions) and facilitators of CC screening (peer support and knowing someone who has screened), we developed the peer advocacy intervention *Game Changers for Cervical Cancer Prevention* (GC-CCP; R21TW011728) as a patient-level implementation strategy to increase CC screening. GC-CCP empowers women who have recently screened for CC to encourage screening among women in their social networks by disseminating CC knowledge, dispelling myths and fears and reducing CC stigma, and facilitating motivation for CC screening. In a pilot randomized controlled trial (RCT) of the peer-led, 7-session group intervention, 40 women who had screened for CC (index participants) were assigned to the intervention (n=20) or wait-list control (n=20), from whom 103 of their social network members (referred to as "alters") who had never screened for CC were enrolled; at month-6, 64% of intervention alters had been screened for CC, compared to just 16% of control alters [OR (95% CI)=12.13 (4.07, 36.16)]. Also, not only did GC-CCP significantly increase CC prevention advocacy among intervention index participants, alters of those in the intervention group (who had no exposure to the intervention, other than indirectly through advocacy from index participants) also reported increased engagement in CC prevention advocacy, compared to controls. The promising results of this pilot, and the strong track record of successful collaboration by our multidisciplinary study team (experts related to CC in the local context, implementation science (IS), and development and evaluation of the network-based peer advocacy intervention), positions this application to make a strong impact on CC prevention and control in Uganda, which could be generalizable to other LMIC settings.

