## Statistical Analysis

**Power:** Assuming 220 1st degree alters per arm enroll, 10% attrition (month 6 retention in pilot was 96%; we have retained 90-94% over 12 months in past studies in Uganda), ICC=.01-.05 range to control for clustering within the alters of each index participant, and a 15% CC screening rate in control alters (based on pilot data): the effective sample size will be 200 (ICC=.05) or 216 (ICC=.01) per arm. If ICC=.01, we will be able to detect a small effect size (11 percentage point difference) in alter CC screening at month 12 (80% power; alpha = .05). If ICC=.05, the detectable effect size is 12 percentage point difference (or odds ratio of 2.0).

**Aim 1:** *Assess effects of GC-CCP on alter CC screening.* We will use an intent-to-treat approach. In addition to comparing the arms at baseline and months 6 and 12, we will apply logistic generalized mixed models to our repeated-measures data to examine intervention effects, using a time by arm interaction to assess differences between the arms over time. We will account for correlation among participants in the same intervention group, and among alters referred by the same index, by adjusting standard errors for statistical inference tests with a sandwich estimator. We will use imputation for item nonresponse and attrition weights to account for non-random dropouts using logistic regression. We will control for and examine interaction effects with index (e.g., age), alter (e.g., knowledge of index's CC screening), and intervention (sessions completed) variables.

**Aim 2:** The analysis for this aim is described in the Preparation and Sustainment phases.

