**Aim 3:** *Examine mediators and moderators of the intervention effects on alter CC screening, and index and alter engagement in CC prevention advocacy.* Potential mediators consist of intervention mechanisms (sharing of CC screening experience, CC knowledge, CC risk management, CC prevention advocacy self-efficacy), while potential moderators include age, history of CC treatment, and network characteristics (e.g., % of alters who are trustworthy). We will explore interactions between a moderator and study arm to examine if the variable moderates the intervention effects. If categorical moderators are significant, we will conduct post-hoc simple main effects t-tests with Bonferroni corrections. For continuous moderators, we will graph significant interactions at low and high levels of each score ( $\pm 1$  SD) and conduct post-hoc simple main effects t-tests with Bonferroni correction by comparing differences between discrete points on the regression lines. To test for mediation, we will run regression models where: (a) the outcome is CC screening measured at month 12 and predictors are intervention indicator, a potential mediator measured at month 6, and covariates, if any; and (b) the outcome is the same potential mediator measured at month 6 and predictors are the intervention indicator and covariates, if any. We will apply a bootstrapping approach to the results from those two models to test whether mediators account for effects, using SAS Proc Causalmed.

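### The Aim 3 mediation model assumes without a check that each mediator acts equally in both arms; if it does not, the indirect effect does not describe the intervention arm

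*Protocol*

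**What the plan says.** The Statistical Analysis section, Aim 3, sets out two regressions. In the outcome model, for screening at month 12, the "predictors are intervention indicator, a potential mediator measured at month 6, and covariates, if any". In the mediator model, "the outcome is the same potential mediator measured at month 6 and predictors are the intervention indicator and covariates, if any". Inference follows directly: "We will apply a bootstrapping approach to the results from those two models to test whether mediators account for effects", "using SAS Proc Causalmed".

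The same paragraph plans arm interactions, but only for moderators: "We will explore interactions between a moderator and study arm to examine if the variable moderates the intervention effects". It lists the moderators (age, treatment history, network characteristics) separately from the mediators (sharing of the screening experience, knowledge, risk management, advocacy self-efficacy). The interactions under Aim 1 concern the screening effect itself and do not enter the mediation model. The protocol neither states nor justifies the assumption that a mediator has the same slope in both arms.

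**The concern.** Leaving out the product of arm and mediator is a modelling assumption: one unit of knowledge, sharing or self-efficacy changes the odds of screening equally in both arms. There is reason to want a check here. Section B argues that effective advocacy needs training. The session outline in D.2.2 teaches disclosure decisions, network use and communication skills, and the control arm receives none of this until after the month-12 follow-up. The training may raise the mediators, and it may also change what a given level of them achieves. The planned pair of models captures the first and cannot show the second.

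If the slopes differ, the single fitted slope is a weighted average over the arms. The indirect effect built from it then understates or overstates the mechanism in the arm that received the intervention. What is at stake is the Aim 3 account of how GC-CCP worked, not whether it worked.

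**Working it through.** The protocol gives no figure for the mediation analysis, so there is none to reproduce.

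**Inputs from the protocol**
- Alters per arm: 220 enrolled, 10% attrition, so 220 × 0.90 = 198 (Statistical Analysis, Power; Section F).
- Control screening: "a 15% CC screening rate in control alters (based on pilot data").
- Intervention screening: 15% + 12 points = 27%, using the detectable difference stated for ICC = .05.

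**Assumptions (not in the protocol)**
- The mediator M is measured on each alter and is normal with SD 1, with mean 0 in controls and 0.5 in the intervention arm.
- Log-odds slopes per SD are b0 (control) and b1 (intervention), varied below.
- No clustering by index participant.

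**Formulas**
- Truth: logit P(screened | arm g, M) = c_g + b_g·M, with c_g solved so that the arm totals are 15% and 27%.
- True indirect effect in the intervention arm: E[expit(c1 + b1·M1)] − E[expit(c1 + b1·M0)], where M1 and M0 are the mediator distributions in the intervention and control arms. The first term is 27% by construction.
- Planned model: logit P = α + β·arm + γ·M, with one γ for both arms. Its indirect effect is the same difference with α + β and γ in place of c1 and b1.

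**Worked case, mechanism only in the intervention arm (b0 = 0, b1 = 0.8).** Solving for 27% gives c1 = −1.527. Moving the mediator back to the control distribution lowers screening to 20.5%, so the true indirect effect is 27.0 − 20.5 = 6.5 points. Fitted to these data, the planned model has a large-sample γ of 0.45, between 0 and 0.8, and an indirect effect of about 4.0 points.

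**Large-sample results, percentage points**

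| b0 | b1 | True, intervention arm | Planned model |
|---|---|---|---|
| 0 | 0.8 | 6.5 | 4.0 |
| 0.4 | 0.8 | 6.5 | 5.4 |
| 0.6 | 0.8 | 6.5 | 6.0 |
| 0.8 | 0.6 | 5.2 | 5.7 |
| 0.8 | 0.8 | 6.5 | 6.5 |
| 0.5 | 0.5 | 4.5 | 4.5 |

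Runs of the 0.4 and 0.8 case gave 5.3 to 5.4. These are limits of the fit, so a larger trial would not remove the gap.

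**Simulated trials, 198 per arm, 95% percentile interval for the product of the two coefficients**
- No slope in either arm: the planned model declares mediation in 4.0% to 4.9% of trials, so the test holds its level.
- Slope 0.8 in the intervention arm only: mediation is declared in about 93-94% of trials by the planned model and 99% or more with the product term. The loss is mainly in the size of the estimate, not in detection.
- Equal slopes, cost of the product term: the standard error of the intervention-arm indirect effect rises from 0.0165 to 0.0181 at slope 0.8 (about 10%), from 0.0146 to 0.0169 at 0.5 (about 16%) and from 0.0127 to 0.0155 at 0.3 (about 22%). Power falls from about 97% to 85% at slope 0.5, and from about 65-66% to 44-49% at slope 0.3.

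**The case against.** The strongest reply is that training raises the mediators, which the mediator model captures, and that no passage says an equally knowledgeable alter behaves differently by arm. Slopes of 0 and 0.8 are an extreme. With 0.6 and 0.8 the gap is half a point. A product term costs precision in a trial sized for Aim 1, and Aim 3 is exploratory. All of this stands. It argues against replacing the planned model, but not against a check, because equal slopes are no better supported by the protocol than unequal ones.

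Three stronger readings are tempting, and the documents do not support them.
- A reader might infer that the plan will declare mediation in the intervention arm when none exists there. This needs a mechanism that works in controls and not at all after training, the reverse of the protocol's theory. With slopes 0.8 and 0 the planned model does give about 2.7 points against a true 0, and mediation is declared in 56% to 67% of runs. But an indirect effect under control conditions is then real (5.3 points), and the stated aim, "to test whether mediators account for effects", does not single out an intervention-arm effect. The test is not invalid in general.
- A reader might infer that results will be odds-ratio indirect effects or percentages mediated, which mislead for a common outcome. Aim 3 names no reporting scale and may leave it to the analysis plan.
- A reader might infer that Aim 3 settles which mechanism carries the effect. The text speaks of examining potential mediators and attaches no decision to the result.

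An analysis plan that is not shown might add the term. The protocol nevertheless fixes the predictors and applies the bootstrap to those two models, so this is more than a detail left open.

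**Conclusion.** The point holds in a limited form. The Aim 3 outcome model fixes a common mediator slope with no check. When the slopes differ, its indirect effect is biased as a description of the intervention arm: about 4.0 points against 6.5 in the extreme case, about 1.1 points too low with slopes 0.4 and 0.8, and about half a point either way for small differences. It is unbiased when the slopes are equal, and the test keeps its level when neither arm has a slope. The direction follows from the algebra. The sizes rest on the assumed mediator shift and slopes, a normal mediator and no clustering. The point touches Aim 3 only and leaves the primary comparison as it is.

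**What to change.** Under Aim 3, keep the planned outcome model and add a second fit that includes the product of arm and mediator. Report natural direct and indirect effects from both fits with the same bootstrap, and state the equal-slope assumption of the first. Say in advance that, where the two disagree, the description of how the mechanism worked in the intervention arm rests on the interaction fit.

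The cost is analysis work and a few lines of text, with no new data. The interaction fit is the less precise of the two, by the amounts shown in the working, and it will miss more weak mechanisms when the slopes are in fact equal. That is the reason to keep the planned model beside it.

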\* **Pilot of Game Changers for CC prevention (GC-CCP):** With an R21, we did formative research to adapt the GC model for CC. Focus groups with women who had and had not screened for CC revealed that like the HIV context, stigma, knowledge, and disclosure were key factors for engagement in advocacy, and thus retained in the intervention model. Internalized stigma did not appear to be an impediment to CC screening per se, but rather stigma and fear acted more as barriers to CC screening disclosure (especially if screened positive), and procedures related to VIA and treatment (e.g., misconceptions that such procedures would harm the vagina and make a woman sterile). A 7-session version of GC-CCP was developed and tested in an RCT with 40 screened women (20 intervention, 20 control) as index participants, from whom 103 alters (58 intervention, 45 control) who had never screened for CC were recruited; all participants were followed for 6 months (with 96% retention). The intervention was feasible and acceptable: peer facilitators were trained to implement the sessions, and 19/20 intervention index participants attended every session.

**Intervention effects on CC screening, CC prevention advocacy, and related outcomes.** In multivariate models controlling for baseline measures of the dependent variable and sociodemographics, alters in the intervention group were much more likely to have been screened for CC at month 6 [64% vs. 16%; adj. OR (95% CI) = 12.13 (4.07, 36.16)], and a higher percentage of alters named in the network assessments of the index survey (360 alters across all index participants; none of whom were perceived to have ever been screened at baseline) were perceived by the index to have been screened at month 6 [57% vs. 14%; adj. beta (SE) = 0.40 (.07);  $p<.001$ ], compared to those in the control. Index participants who perceived an enrolled alter to have screened for CC at month 6, were correct 88% of time. Alters in the intervention arm also reported greater engagement in CC prevention advocacy, CC knowledge, and CC risk management, compared to control alters (all  $p$  values < .001). Intervention index participants reported greater CC prevention advocacy at month 6, as well as greater sharing of CC screening experience, CC knowledge, CC prevention advocacy self-efficacy, and CC risk management (most  $p$  values < .001), compared to index participants in the control group.

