**1st degree alters:** The site coordinator will use the social network assessment within the baseline survey of each index to randomly select (using a random number table) 5 alters who know the participant's CC screening experience (or as many as there are if < 5) and ask the index if she is comfortable recruiting 3 of these alters. The index will be asked to call each selected alter at the end of their baseline interview to describe the study in the presence of the coordinator (or later in private, if she prefers), who will schedule a study visit for the alter. If an alter refuses or cannot be reached, a replacement will be randomly chosen from the original list of 5 alters.

**2nd degree alters:** The site coordinator will use the social network assessment in the month 6 survey of each 1st degree alter to randomly select 4 alters (or as many as there are if < 4) who the alter reports targeting with CC screening advocacy and thereafter was screened for CC. A similar process as described above for 1st degree alters, will be used to recruit and enroll 2nd degree alters. The coordinator will obtain verbal consent from the 2nd degree alter over the phone and the complete a brief 15-minute phone survey.

**Assessment schedule:** Surveys will be administered at baseline, month 6 and month 12 for index and 1st degree alters, and 2nd degree alters will be surveyed only once (at month 6 assessment of 1st degree alters). Participants will receive 30,000 Ush (~\$8) per assessment, except 2nd degree alters who will receive 10,000 Ush (via mobile money). To limit attrition, we will collect tracking information (phone numbers and mapped addresses), including contacts for family/friends with whom they have frequent contact. Clinic staff will help us track clients we have difficulty reaching. In the pilot, >96% of index and alters were retained at month 6.

**Measures:** Survey assessments for index and 1st degree alter participants will be interviewer-administered in Luganda using Network Canvas software, last ~ 75 minutes, and include a social network assessment. CC screening and treatment utilization will be verified with medical chart data.

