## **F. DATA SAFETY AND MONITORING PLAN**

### **I. Description of Study and Study Data**

This study is a partnership among RAND Corporation ([name] and [name], MPIs), Makerere School of Public Health ([name], MPI), African Palliative Care Association, Rays of Hope Hospice Jinja, and Indiana University at Bloomington. We will conduct a hybrid implementation-effectiveness randomized controlled trial (RCT) of *Game Changers for Cervical Cancer Prevention (GC-CCP)*, a 7-session peer-led group intervention that aims to empower and mobilize women who have screened for cervical cancer (CC) to be agents for CC screening and prevention in their social networks. For the RCT, we will recruit 160 screened women (index participants) across 4 clinics, randomizing 80 to the intervention and 80 to the usual care control condition. Each index participant will be asked to recruit up to 3 social network members (1st degree alters) who have never screened for CC to complete assessments (~440 total based on average of 2.75 alters recruited per index participant, 220/arm) over 12 months, to test intervention effects on alter uptake of CC screening. All participants will complete surveys at baseline, and 6- and 12-months post-baseline. At the

month 6 follow-up, first degree alters will be asked to recruit up to 2 of their social network members (2nd degree alters; ~ 800 total). Surveys of index and alter participants will include questions about CC screening, CC knowledge, CC stigma, and engagement in CC prevention advocacy. Data on alter CC screening and treatment will be extracted from medical records. All data will be collected and stored at the participating clinic sites initially, and then transferred to Makerere University School of Public Health; de-identified data will be transferred to RAND for data management and analysis.

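### The Aim 3 mediation models do not require the baseline value of the mediator, so a scale can be reported as a mediator only because its baseline level predicts screening

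*Protocol*

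**What the plan says.** The Aim 3 paragraph of the protocol's Statistical Analysis section gives the mediation analysis in model form.

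- Model (a), for screening: "the outcome is CC screening measured at month 12 and predictors are intervention indicator, a potential mediator measured at month 6, and covariates, if any".
- Model (b), for the mediator: "the outcome is the same potential mediator measured at month 6 and predictors are the intervention indicator and covariates, if any".

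A bootstrap is then applied to the two models together. The mechanisms to be tested are listed: "Potential mediators consist of intervention mechanisms (sharing of CC screening experience, CC knowledge, CC risk management, CC prevention advocacy self-efficacy".

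The baseline data exist. The assessment schedule in D2.2.1 states: "Surveys will be administered at baseline, month 6 and month 12 for index and" first-degree alters. The mediator scales are in the Survey Constructs table, and the data and safety monitoring section says: "Surveys of index and alter participants will include questions about CC screening, CC knowledge, CC stigma, and engagement in CC prevention advocacy".

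For the pilot, D.1 Preliminary Studies reports effects estimated as follows: "In multivariate models controlling for baseline measures of the dependent variable and sociodemographics".

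**The concern.** Arm is randomised; the month-6 mediator is not. A woman who enters with more knowledge or self-efficacy will tend to have more at month 6, and may also be readier to be screened whatever the programme does. If model (a) holds only arm and the month-6 scale, that pre-existing difference loads onto the mediator coefficient.

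The other half of a mediation finding, an arm effect on the scale, is likely to be present. The pilot reported intervention effects on knowledge and risk management in alters, and on sharing, knowledge, advocacy self-efficacy and risk management in index participants. A real first path combined with a confounded second path gives a false indirect effect.

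Aim 3 is meant to show which mechanisms carry the effect on screening, so a false mediator would misdirect later versions of the training.

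**Working it through.** The protocol gives no figure for the mediation analysis, so there is none to reproduce. The check asks how much the missing baseline term could matter.

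**Inputs from the protocol.** 220 first-degree alters per arm with 10% attrition, so 220 × 0.9 = 198 per arm; 15% screening in controls; ICC up to 0.05; 2.75 alters per index; alpha 0.05.

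**Assumed inputs, not in the protocol.** Correlation ρ between baseline and month-6 mediator of 0.3, 0.5 or 0.7; arm effect on the mediator a = 0.5 SD; log odds ratio g of screening per SD of baseline mediator of 0.3 or 0.5 (odds ratios of about 1.35 and 1.65); arm log odds ratio 0.7 (about 2.0).

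**Step 1: expected bias.** Take M6 = a·arm + ρ·M0 + √(1−ρ²)·e, where M0 is baseline and has unit variance. Let screening depend on arm and M0 but not on M6. Within arm, M6 has variance 1 and covariance ρ with M0, so omitting M0 gives M6 a spurious coefficient of about ρ·g. The spurious indirect effect is about a·ρ·g.

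**Step 2: simulation.** 198 alters per arm and 2,000 trials per setting. The mediator model was linear and the screening model logistic with intercept −1.8 (1/(1+e^1.8) = 14% at average baseline). The 95% interval for the indirect effect came from the distribution of the product, standing in for the planned bootstrap. Clustering was ignored here. The true mediator effect is zero.

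| ρ | g | a·ρ·g | simulated spurious effect | false mediation, baseline omitted | baseline in both models |
|---|---|---|---|---|---|
| 0.3 | 0.3 | 0.045 | 0.046 | 11.5% | 5.3% |
| 0.3 | 0.5 | 0.075 | 0.071 | 20.8% | 5.5% |
| 0.5 | 0.3 | 0.075 | 0.075 | 21.2% | 5.2% |
| 0.5 | 0.5 | 0.125 | 0.123 | 49.8% | 5.0% |
| 0.7 | 0.3 | 0.105 | 0.108 | 39.1% | 4.8% |
| 0.7 | 0.5 | 0.175 | 0.177 | 78.4% | 5.2% |

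The formula and the simulation agree.

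**Step 3: where the problem vanishes.** With a = 0, ρ = 0.5 and g = 0.5, false mediation is 1.5% without the baseline term. In a second set of settings (a = 0.6 SD, arm odds ratio 3, ρ = 0.5, both paths required at p < 0.05), a baseline odds ratio of 1.1 gives 7.5% unadjusted against 4.8% adjusted. Odds ratios of 1.25, 1.5 and 2.0 give 16%, 37% and 78%, against about 5% adjusted.

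**Step 4: clustering.** Those three settings, repeated with baseline clustered by index (ICC 0.05, about 3 alters per index, cluster-robust errors), give 16.5%, 39% and 77.5% unadjusted and 4.5% to 7% adjusted. Ignoring clustering does not explain the result.

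**Step 5: power.** For the arm-to-mediator path, retained cluster size is 2.75 × 0.9 = 2.475 and the design effect is 1 + 1.475 × 0.05 = 1.074, so the effective n is 198/1.074 = 184 per arm. For a 0.3 SD effect, power is 82.1% unadjusted. With residual SD √(1−ρ²) it is 85.5%, 91.4% and 98.1% at ρ = 0.3, 0.5 and 0.7.

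For the whole indirect effect (a = 0.3 SD, mediator log odds ratio 0.4, baseline with no direct effect on screening):

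| ρ | unadjusted | adjusted |
|---|---|---|
| 0.3 | 69.8% | 69.2% |
| 0.5 | 71.3% | 68.1% |
| 0.7 | 72.0% | 59.0% |

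Adjustment leaves only 1−ρ² of the mediator variance (0.91, 0.75, 0.51) to estimate its effect in model (a). This offsets the gain in model (b).

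**The case against.** The strongest reply is that both models carry an open covariate term, so the protocol does not exclude the baseline scale. A statistical analysis plan, not shown here, could name it, and covariate lists are often left to that document. The pilot practice also makes a model with no covariates less likely. This stands as far as it goes: a reader might infer that the plan rules out baseline adjustment, and the text does not support that. But the protocol does more than defer. It sets out both regressions and names the required predictors, and the analysis without the baseline value complies with it.

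A reader might also infer that omitting the baseline costs power for the mediation test. It does not. The precision gain is confined to the arm-to-mediator path; power for the indirect effect does not rise and can fall.

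The magnitudes rest on assumed correlations and baseline effects that no part of the protocol supplies. In every false-mediation setting the baseline level predicts screening while the month-6 level has no effect. With a weak baseline association the excess is small. That limits the figures to an illustration of risk and leaves the direction of the bias unchanged.

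Finally, not every mediator has a usable baseline. First-degree alters enter with no screening history, so sharing their own screening experience has no meaningful baseline value in them. The point does not extend to that scale in alters.

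**Conclusion.** The point holds in a limited form. As written, Aim 3 permits mediation models without the baseline mediator, and those models can confound the mediator-to-screening path. Over the assumed range (ρ 0.3 to 0.7, baseline log odds ratio 0.3 to 0.5 per SD, arm effect 0.5 SD) false mediation runs from about 12% to 78%, against about 5% with the baseline term. It is close to or below the nominal 5% when baseline hardly predicts screening or the arm does not move the scale. The adjusted figures assume that baseline is the only confounder, so the term reduces confounding but cannot be taken to remove all of it.

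The arm-to-mediator path is protected by randomisation and is not biased; it is only less precise than it could be. The Aim 1 comparison of screening between arms is untouched. This concerns a secondary, explanatory aim.

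**What to change.** In the Aim 3 paragraph, state that the baseline value of the same mediator enters as a predictor in both model (a) and model (b), for index and alter scales alike, wherever a baseline measure exists. State the one exception: sharing of one's own screening experience in never-screened alters, where the term is left out.

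The cost is one sentence and one covariate per model, with no new data. Missing baseline items can be handled by carrying over the item imputation already described under Aim 1. The price to accept is some power for the indirect effect, most at high correlation: 72.0% to 59.0% at ρ = 0.7 if baseline has no direct effect on screening.

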**Aim 4.** *Evaluate the cost and cost-effectiveness of implementing GC-CCP to increase CC screening and early-stage treatment.* We will compare GC-CCP vs. enhanced usual care on the marginal cost of increasing alter CC screening. Following standard convention, we will define the incremental cost-effectiveness ratio (ICER) as the difference in per-capita cost of the intervention versus control group divided by the difference in their average effectiveness:  $ICER = \frac{\mu_{C2} - \mu_{C1}}{\delta_{e2} - \delta_{e1}}$  ( $\mu_{C2}$  = mean per-capita cost of GC-CCP,  $\mu_{C1}$  = mean per-capita cost of usual care,  $\delta_{e2}$  = % of alters who get screened in GC-CCP,  $\delta_{e1}$  = % of alters who get screened in enhanced usual care). We will estimate confidence intervals with bootstrap methods. We will examine economic costs from a societal perspective, incorporating estimates of the frequency and duration of time spent by individuals engaging in receipt of services, as well as transportation costs and forgone employment as relevant. We will use a micro-costing approach, time-driven activity based costing (TDABC), to track all costs associated with implementing GC-CCP and enhanced usual care as estimated from data collected by the sites and study team. The cost per resource will be calculated by multiplying the quantity used by unit cost; total cost will be derived by summing individual costs. Capital costs will be annualized using a discount rate of 3% with an assumed lifespan of 30 (buildings) and 10 (furniture) years. Facilitators will record time spent on the sessions, identifying each activity (e.g., training, preparation, in-session) and session-related materials (e.g., consumable materials). Unit costs for labor will be characterized as capacity cost rates, as described in standard TDABC methodology. Intervention development (training) and ongoing costs will be differentiated; ongoing costs will be tracked to determine cost efficiencies over time, and we will differentiate fixed from variable intervention costs to assess the marginal cost of providing care to additional clients.

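### The Aim 3 mediation bootstrap makes no provision for alters nested within index women; if single alters are resampled, intervals for index-level mediators would be materially too narrow

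*Protocol*

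**What the plan says.** All of this is in the Protocol, Statistical Analysis.

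- **Power.** The calculation allows for "ICC=.01-.05 range to control for clustering within the alters of each index participant".
- **Aim 1.** The plan states "We will account for correlation among participants in the same intervention group, and among alters referred by the same index", and does so "by adjusting standard errors for statistical inference tests with a sandwich estimator". The sentence is written for the Aim 1 mixed models.
- **Aim 3.** "To test for mediation, we will run regression models where: (a) the outcome is CC screening measured at month 12", with the arm indicator, a month-6 mediator and any covariates as predictors. A second model regresses that mediator on arm and covariates. Then: "We will apply a bootstrapping approach to the results from those two models to test whether mediators account for effects", "using SAS Proc Causalmed". Clustering is not mentioned.
- **Aim 4.** For the ICER: "We will estimate confidence intervals with bootstrap methods". Nothing more is said about resampling.

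Section A (Specific Aims, aim 3) looks for mediators and moderators among index, alter and network characteristics, with alter screening as one of the outcomes.

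**The concern.** The Aim 3 text is not a general statement of intent. It fixes the two models, their predictors and the procedure, and it leaves out the dependence that Aim 1 corrects for in the same women. An analyst following it literally would have one row per alter and a bootstrap over rows.

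That matters most when the mediator belongs to the index woman. Her score is then copied onto each of her alters, and resampling rows treats the copies as separate observations. The indirect effect would look more precise than it is, and a mechanism could be declared when there is none. Aim 3 is where the trial explains how the intervention works, so false precision there affects its main explanatory claims.

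**Working it through.** **Inputs.** From Statistical Analysis, Power: "Assuming 220 1 st degree alters per arm enroll, 10% attrition", and index ICC .01-.05. From section F, part I: a mean of 2.75 alters per index. From D2.2.1: at most 3 alters per index, 80 index women per arm, and intervention groups of 10, two at each of four sites (8 groups).

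**1. The plan's own figure.** Effective size = n / (1 + (m - 1) x ICC). With n = 220 and m = 3: 220/1.10 = 200 at ICC .05, and 220/1.02 = 216 at ICC .01. Both stated figures reproduce, so the plan itself treats alters of one index as correlated. (They reproduce only without the 10% attrition, which is a separate matter.)

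**2. Retained alters.** 2.75 x 0.9 = 2.475 per index; 160 x 2.475 = 396 in all.

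**3. Index-level mediator, arm-to-mediator path.** The mediator is identical for all alters of one index, so its within-index correlation is 1.
- Design effect = 1 + (2.475 - 1) x 1 = 2.475.
- Alter-level SE / correct SE = 1/sqrt(2.475) = 0.636, about 36% too small.
- Coverage for this path = 2 x Phi(1.96 x 0.636) - 1 = about 79%.
- Equivalent information: 396/2.475 = 160 index women, not 396 alters.

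This step needs no assumed ICC.

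**4. Index-level mediator, indirect effect.** Write A for the arm-to-mediator coefficient and B for the mediator-to-screening coefficient. Approximately, Var(AB) = B² Var(A) + A² Var(B). Only the first term carries the factor 2.475. The second carries about 1 + 1.475 x ICC, which is 1.015 to 1.074. The loss therefore depends on the effect sizes, and simulation is needed.

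One illustrative simulation used 160 index women, a mean of 2.475 alters, outcome ICC .05, 15% base rate, a linear probability model, 400 replicates and assumed effects.

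| Truth | Alter resampling, coverage | Index resampling, coverage |
|---|---|---|
| No arm effect on the mediator | 76% (mean SE .0085, true SD .0130) | 93% (mean SE .0134) |
| Real indirect effect | 82% | 91% |

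The first row means about 24% false positives. A second check gave about 72-84% for alter resampling and 92-94% for index resampling.

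**5. Alter-level mediator.** Apply the protocol's ICC of .01-.05 with m = 2.475 to 3. The design effect runs from 1.015 to 1.10, 1/sqrt gives intervals 0.7% to 4.7% too narrow, and coverage is 94.8% to 93.8%. This is the formula for an arm difference. A direct simulation of the indirect effect (200 replicates) found alter-level SEs within 1% of index-level SEs over this ICC range.

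**6. Intervention groups.** The protocol gives no group ICC, so these values are assumptions. There are 220/8 = 27.5 alters per group, in the intervention arm only. For example, with group and index ICC both .01 and screening of 27% against 15%:
- Intervention-arm design effect = 1 + 1.75 x .01 + 24.75 x .01 = 1.265; control-arm design effect = 1.0175.
- Width ratio = sqrt[(.1971 + .1275) / (.1971 x 1.265 + .1275 x 1.0175)] = 0.925.

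Over index ICC .01-.05, the interval for the arm difference is about 7-10% too narrow at group ICC .01, 13-15% at .02 and 26% at .05.

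**The case against.** The strongest objection is that the protocol does not say single alters will be resampled. It is silent on the unit. A resampling unit for secondary mediation and cost analyses is often left to the statistical analysis plan, and Aim 1 shows that the team knows both levels of clustering. A reader might infer that both bootstraps ignore clustering and that their intervals are too narrow. The text does not support that as fact, so the point is conditional. It stands for Aim 3 because that method is written out to the software level and the adjustment is missing from what is written. What the named procedure can resample is not stated in the protocol, and the point does not rely on it.

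The mediator scales are in surveys given to both index women and alters, and Aim 3 does not say whose score enters the model. So the large loss applies only where the index woman's score is used. But the Specific Aims name index characteristics. Sharing of one's screening experience is naturally an index variable, because first-degree alters enter with no screening history.

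A reader might also infer a fault in the ICER interval because session costs are shared by a group. Aim 4's single general sentence cannot show one. Costs there also include individual time, transport and lost work, and the text does not say how cost enters the bootstrap.

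**Conclusion.** The point holds for Aim 3 in conditional form. As written, the mediation analysis omits the nesting of alters within index women. Resampling single alters would then materially understate uncertainty for index-level mediators: an SE about 36% too small on the arm-to-mediator path, and illustrative coverage of the indirect effect of about 72-84%. The path figure rests on 2.475 retained alters per index and on the index woman's score being the mediator. The coverage range also rests on assumed effect sizes and an outcome ICC of .05; the loss is smaller when uncertainty in the mediator-to-screening path dominates.

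For alter-level mediators the loss is negligible to small (coverage about 94-95%), if the protocol's ICC for screening also describes the mediator. A large loss from group clustering might be inferred, but it depends on a group ICC that the protocol does not supply. No error is shown for the ICER, and the primary analysis is not affected.

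**What to change.** State under Aim 3 that the mediation bootstrap draws whole index women with all their alters, within site and arm, instead of single alters. Say for each mediator whether the index woman's or the alter's score is used. Under Aim 4, name the same resampling unit for the ICER interval, for consistency.

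Do not resample intervention groups within site. With two groups per site, a bootstrap reproduces only about (2 - 1)/2 = half of the between-group variance, so its intervals would themselves be too narrow.

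The cost is a short custom bootstrap program and somewhat wider intervals, mainly for index-level mediators. No new data are needed.
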